## Abstract

**Background:**

Self-expanding nitinol stents must be oversized at least by a minimal amount to ensure contact with the vessel wall and prevent migration. Once the stent is deployed it exerts a continuous force upon the vascular wall, termed chronic outward force (COF). Animal studies have found an increased neointimal hyperplasia in stents with high oversizing and thus high COF. Data about correlation between COF and neointimal hyperplasia in humans are currently lacking. The objective of the BIOFLEX-COF trial is to prospectively investigate differences in formation of intimal hyperplasia at 1 and 2 years after implantation of nitinol stents with high versus low COF in de novo femoropopliteal occlusive arterial lesions.

**Methods:**

The BIOFLEX-COF trial is a prospective, quantitative, randomized study. Eighty subjects with symptomatic peripheral arterial lesions eligible for endovascular stent implantation will be enrolled and randomly assigned to either a high COF group (LifeStent Flexstar, Bard Peripheral Vascular Inc., Tempe, AZ, USA) or low COF group (Pulsar, Biotronik AG, Bülach, Switzerland) using an online randomization program to generate a random 1:1 group allocation (block randomization). After implantation and dilatation, COF at every 2 mm along the stent axis will be calculated from the actual stent diameter versus its nominal diameter.

There will be two follow-up evaluations at 12 and 24 months. Primary endpoint is the amount of in-stent neointima at 1 year, assessed by contrast-enhanced CT angiography (CTA). In the control examinations, stent diameter and true lumen diameter will be measured on DICOM images every 2 mm along the stent axis to quantify the relative amount of in-stent restenosis.

Secondary objectives are the amount of in-stent neointima at 2 years, device- and procedure-related adverse events and target lesion revascularization (TLR) rate.

The scheduled time for recruitment is 2 years. Recruitment is expected to be complete in October 2017.

**Discussion:**

This trial is the first to prospectively investigate the influence of COF on stent patency. If successful, the results will aid in a more precise selection of stent type and size in a given target vessel.

The present study is challenging in that it compares two different self-expanding nitinol stents head-to-head against each other. To optimize the power of this study, traditional binary outcome parameters such as TLR and restenosis at Doppler ultrasound were dropped as primary endpoints. Instead, the amount of neointima inside the stent accessed by CTA was selected as (continuous) outcome parameter.

**Trial registration:**

ClinicalTrials.gov Identifier: NCT03097679. Date of registration: 14 March 2017 (retrospectively registered).

**Electronic supplementary material:**

The online version of this article (doi:10.1186/s13063-017-2338-0) contains supplementary material, which is available to authorized users.

## Background

Arterial occlusive disease in the femoropopliteal segment can be re-vascularized in an open surgical or an endovascular approach. While the surgical techniques have been optimized previously and not undergone extensive changes over the last years, endovascular techniques have been characterized by rapid revolution of a broad variety of endovascular devices that facilitate vascular access, lesion recanalization, and treatment efficacy. Simple balloon angioplasty was complemented by stent deployment and a multitude of other technologies, and reported patencies were constantly increasing. Third-generation nitinol stents show markedly improved patency compared to their early predecessors and are today used alongside stent grafts [1], drug-eluting stents and drug-coated balloons. This ever-increasing efficacy and safety of endovascular treatment in the femoropopliteal segment was reflected both in clinical practice, scientific research data, society recommendations, and patient preference by allocating ever more severe occlusive lesions to an “endo-first” strategy [2].

Unfortunately, the introduction of many new endovascular devices and techniques did not lead to a sufficient body of scientific evidence (let alone level 1 evidence) that would aid in the decision when and how to use it and which one to prefer over another. For example, indications that primary nitinol stenting is superior to balloon angioplasty and provisional stenting is based on solely three randomized control trials (RCTs) that showed superiority of primary stenting [3–5] and one RCT that showed a trend to increased patency in the stent group in short lesions [6]. The notion that drug eluting-stents might be superior to plain nitinol stents is currently based on only a single RCT in which a secondary randomization was performed between nitinol stent and drug-eluting stent after failed balloon angioplasty [7] although more studies are ongoing. Lastly, there exists not a single randomized study comparing primary nitinol stenting versus drug-covered balloon angioplasty to this day. Despite this, many researchers advocate drug-covered balloons over nitinol stents as treatment of choice in shorter lesions [8–10].

The current study was planned out of a desire for more insight in how to optimally select and size a nitinol stent in the femoropopliteal segment. In contrast to drug-coated balloons or bio-absorbable devices, nitinol stents will interact with the vessel wall for the whole duration of their patency. Since nitinol stents are self-expanding, they must be oversized at least by a minimal amount to ensure contact with the vessel wall and prevent migration. Once the stent is thus deployed, the stent struts exert a continuous force upon the vascular wall, termed chronic outward force (COF) [11, 12], see Fig. 1.

**Fig. 1 Fig1:**
[figure not shown]
Concept of chronic outward force (COF)

If in cases where the artery is compressed circumferentially from the outside (such as in the adductor canal) an even higher force between the stent and the vessel wall needs to be effected before the stent gives way to the external compression and is temporarily compressed. This force is called radial resistive force (RRF), see Fig. 2.

**Fig. 2 Fig2:**
[figure not shown]
Concept of radial resistive force (RRF)

Chronic outward force depends on two factors: (i) the oversizing of the stent compared to the diameter of the target vessel (i.e., how much bigger is the nominal diameter of the stent compared to the vessel) and (ii) the spring constant (“stiffness”) of the stent material (i.e., how steep the COF increases if the stent is not allowed to expand fully to its nominal diameter) [11]. In several animal studies, groups with high versus low oversizing of self-expanding nitinol stents have been compared. The majority of the studies found a markedly increased neointimal hyperplasia in the group with high oversizing and thus high COF [13–16]. However, two studies found no significant difference between study groups [17, 18].

Data about COF and neointimal hyperplasia in humans are currently lacking. There is only one post hoc analysis of data from the VIPER study [19] that investigated patency after implantation of stent-grafts in the superficial femoral artery (SFA). At the time of the study the smallest available device was 6 mm in diameter and was implanted in vessels between 3 and 4 mm in diameter, resulting in an unusually high degree of stent oversizing. A subgroup analysis of this study collective revealed that patients with stent-grafts which had been oversized by more than 20% had 70% patency at 1 year, whereas patients with oversizing below 20% had 88% patency at 1 year (*p* = 0.047).

The objective of the BIOFLEX-COF trial is to investigate differences in formation of intimal hyperplasia at 1 and 2 years after implantation of nitinol-stents with high versus low COF in de novo femoropopliteal occlusive lesions in patients with symptomatic peripheral arterial disease. The low COF group will receive a thin strut-stent with marginal oversizing, whereas the high COF group will receive a thicker strut, stiff-stent with generous oversizing. All employed stent types and sizes are approved for clinical use for the respective anatomical sides, lesions, and indications.

## Methods

### Study design

The BIOFLEX-COF trial is a monocentric, prospective, quantitative, randomized study which received approval from the Ethics Committee of the Medical University of Vienna (EK Nr. 1026/2015, Ver.5.0, October 2015). The study site is the General Hospital of Vienna of the Medical University of Vienna. The protocol was drafted by the authors of the current manuscript; the sponsor is the Medical University of Vienna, [name]. Patient recruitment started in October 2015. The recruitment period is estimated to be for 24 months, the follow-up period is estimated at 24 months. Figure 3 shows a flow diagram of the study design.

**Fig. 3 Fig3:**
[figure not shown]
Flow diagram of the study design

### Stent types

The low COF group receives a thin-strut stent (Pulsar, Biotronik AG, Bülach, Switzerland) with minimal oversizing (according to manufacturer’s instructions), the high COF group receives a stiffer stent (Lifestent Flexstar, Bard Peripheral Vascular Inc., Tempe, AZ, USA) with maximal oversizing (according to manufacturer’s instructions). The stent sizing is based on group allocation and SFA diameter measurements according to a sizing table (Table 1, showing the device sizing according to the vessel diameter). The Pulsar-18 is a laser-cut self-expanding nitinol stent loaded on a low-profile 4 F compatible over-the-wire coaxial delivery system. The stent has a flexible, thin-strut, open-cell design with helically aligned peak-to-valley crowns and six radiopaque markers at each end. It is completely covered with an amorphous silicon carbide coating.

**Table 1 Tab1:** Stent diameter used according to the vessel diameter

		Nominal stent diameter (mm)		
Vessel diameter (mm)	Pre-dilatation	LifeStent	Pulsar-18	Post-dilatation
4–4.5	3	6	4	4
4.6–5.5	4	6	5	5
5.6–6.5	5	7	6	6
6.6–7.0	6	8	7	7

The LifeStent Vascular Stent System is comprised of the LifeStent Vascular Stent (stents 20–80 mm) and the LifeStent XL Vascular Stent (stents 100–170 mm). The devices contain self-expanding, flexible, nitinol stents that expand to a preset diameter upon exposure to body temperature. The stents are equivalent to one another in design with only one difference located at the crown section; the LifeStent contain six tantalum radiopaque markers on both the distal and proximal ends of the stent, while the LifeStent XL stent does not have markers. Figure 4 shows the two stent types in detail.

**Fig. 4 Fig4:**
[figure not shown]
Chronic outward force of different stent fabricates according to stent diameter

The two stent choices were based on bench test data provided by Biotronik AG on SFA stents from various manufacturers. Using these curves, the COF of each stent can be determined for every diameter below its nominal diameter. The LifeStent shows the steepest COF curve, while the AstronPulsar stent shows the flattest curve. When comparing both stents at a size of 6 × 100 mm the mean values for maximum and minimum RRF are lower for the Pulsar-18 compared to the LifeStent (0.464 and 0.413 N/mm^2^ vs. 1.160 and 1.059 N/mm^2^). Also mean values of maximum and minimum COF are lower for the Pulsar-18 compared to the LifeStent (0.313 and 0.249 N/mm^2^ vs. 0.732 and 0.575 N/mm^2^). The strut dimensions of the Pulsar-18 are 139 × 90 μm compared to 192 × 102 μm for the LifeStent.

### Primary endpoint

Primary endpoint is the amount of in-stent neointima at 1 year, assessed by contrast-enhanced CT angiography (CTA). The volume of neointima inside the stent will be calculated by measuring every 2 mm along the longitudinal axis of the stent: (i) the diameter of the stent in two perpendicular directions and (ii) the diameter of the contrast-enhanced lumen in two perpendicular directions. The difference between these two measurements represents the thickness of the neointima, which will be represented relative to (as percentage of) the stent diameter.

### Secondary objectives

Secondary objectives are the amount of in-stent neointima at 2 years, device- and procedure-related adverse events according to ISO 14155:2011 and target lesion revascularization (TLR) rate. In patients undergoing TLR the amount of in-stent neointima will be assessed by calibrated quantitative angiography at the time of the secondary intervention since no CT angiography will be available for these patients.

Technical success defined as successful stent deployment and absence of significant residual stenosis as well as patent in- and outflow at completion angiography.

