### Procedure

Vascular access is performed at the investigators discretion under local anesthesia, sedation, or general anesthesia. A contralateral or ipsilateral approach is permissible. A bolus of 5000 units of heparin is administered i.v. Diagnostic angiography is performed from the groin to the ankle (from the aortic bifurcation if no non-invasive imaging is available to document the patency of the inflow). Endovascular treatment of stenosed inflow (including the SFA orifice) and (after successful index lesion transversal) outflow lesions is permissible.

After successful lesion transversal and confirmation of inflow and outflow patency, the patient will be randomized one-to-one by a clinical research assistant (CRA). For this purpose, an online randomization program (www.sealedenvelope.com) will be used to generate a random 1:1 group allocation (block randomization). Only one limb is eligible for inclusion in the study.

A radiopaque calibrated ruler will be present on all radiographic images. Diameter measurements of the proximal and distal landing zone in a un-diseased SFA segment will be performed. These measurements will be used to select the balloon size for pre- and post-dilatation as well as the stent size according to the manufacturers’ stent-sizing table. After pre-dilatation with a subdiameter PTA balloon for 1 minute, the stent will be deployed and the post-dilated. The diameters for the pre- and post-dilatation balloon and the stent diameter will be determined after measuring the diameter of the non-diseased SFA at the proximal end of the intended treatment site. Table 1 gives the respective diameters of the stents for different SFA diameter ranges.

Stents will be deployed beginning with the most distal site. Spot-stenting of multiple lesions is permissible. Any balloon pre-dilated lesion should be covered by the device. Incomplete covered areas, if present, will be evaluated separately.

Stents will be assessed for correct implantation length by observing the relative proximal and distal stent markers with the corresponding delivery system markers. Deviations will be recorded as millimeter elongation or compression.

Completion angiography will be performed from the groin to the ankle (aortic bifurcation to ankle if inflow lesion treatment has been performed). After confirmation of absence of relevant residual stenosis the wire will be removed and radiography of the stent will be performed in two planes differing by ≥ 30 degrees.

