### CTA

Patients will be scheduled for two CTA control examinations, after 12 and after 24 months. Stent diameter and true lumen diameter will be measured on DICOM images every 2 mm along the stent axis to quantify the relative amount of in-stent restenosis as:$$ \%\kern0.5em Restenosis\kern0.5em =\kern0.5em \frac{D_s-{d}_l}{D_s}\times 100 $$

(D_s_ = stent diameter, D_l_ = lumen diameter)

For patients who receive target lesion revascularization or bypass surgery, the pre-operative CTA or angiography will be used to determine the amount of in-stent neointima at the time of the re-intervention.

All metallic stents generate some kind of blooming artifacts at CT imaging with a big variation between the different available stents. To face this issue, several techniques for CT imaging and reconstruction have been proposed, and most of them will be combined in the present study. In this trial, CT angiographies will be obtained with a third-generation Dual Source scanner, and the highest possible spatial resolution will be obtained, since blooming artifacts decrease with increased spatial resolution. Slice collimation will be 2 × 64 × 0.6 mm, and matrix size will be 512 × 512 pixels. Furthermore, image raw data will be reconstructed under application of an iterative reconstruction technique (Advanced Modeled Iterative Reconstruction - ADMIRE) and using a dedicated edge-enhancing kernel. Finally, the three-dimensional reconstruction of multipath-centered curved planar reformations (mCPR) will further facilitate the almost artifact-free assessment of the in-stent lumen.

All measurements will be undertaken on dedicated PACS stations (IMPACS EE R20 XVI SU1, AGFA Healthcare, Mortsel, Belgium) by two independent investigators with a minimum experience of 4 years with the software, blinded to patient and clinical information and group allocation.

Figure 5 shows the schedule of enrolment, all interventions and assessments.

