### Trial management and quality assurance

A CRA will perform regular monitoring sessions and interim analyses every 6 months (independent from study investigators and sponsor), in which protocol compliance and correctness of data will be assessed. The CRA will have direct access to medical records, radiographic images, the hospital information system, and all study material for source data verification, will report all serious adverse events (SAEs) to the institutional ethics committee in accordance with all legal and institutional requirements. Case report forms (CRFs) will be generated and stored at the study site. Adherence to the follow-up investigation schedule will be promoted by mailing reminders to the patient 1 month in advance. In addition, the CRA will perform continuous monitoring for adverse events during the study period using the above-mentioned resources and report adverse events and other unintended effects of trial interventions or trial conduct to the institutional ethics committee, which under applicable law has the authority to terminate the trial. Potential relevant protocol modifications must be communicated to the ethics committee and will be communicated to this journal. Confidentiality of personal information will be provided by (a) keeping all documents containing personalized information strictly on site and accessible only by authorized personnel bound by written obligation to confidentiality, (b) anonymizing patient data in the CRFs and the data analysis files. All authors will have unlimited access to the final trial dataset and did not enter agreements that limit such access. Additional file 2 shows the SPIRIT 2013 Checklist as recommended for clinical trial protocols.

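### The only adverse-event outcome named is limited to device- and procedure-related events, so a judgement with no described masking decides which events enter it

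*Protocol article*

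**What the plan says.** The Secondary objectives section lists neointima at 2 years, "device- and procedure-related adverse events according to ISO 14155:2011", and the TLR rate. The Abstract (Methods) carries the same restriction to related events. Neither place, nor any other section, names all adverse events or all serious adverse events (SAEs) as an outcome.

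The following passages bear on who knows the arm and which events are captured:

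- Stent types: "The stent sizing is based on group allocation and SFA diameter measurements according to a sizing table". The two arms receive different devices.
- Procedure: "the patient will be randomized one-to-one by a clinical research assistant (CRA").
- Trial management and quality assurance: "the CRA will perform continuous monitoring for adverse events during the study period". The same section says the CRA "will report all serious adverse events (SAEs) to the institutional ethics committee" and will "report adverse events and other unintended effects of trial interventions or trial conduct to the institutional ethics committee". None of this is limited to related events.
- CTA: the two image readers are "blinded to patient and clinical information and group allocation". This is the only blinding described in the article.

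**The concern.** Calling an event device- or procedure-related is a judgement made after randomisation. When the outcome admits only events so judged, that judgement acts as its entry filter. If it is made with the arm known, a difference in how readily events are attributed to one stent can create a difference between arms or hide a real one. A count of all events by randomised arm does not pass through that filter.

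The article accepts the principle elsewhere. Its Discussion demotes TLR from primary endpoint partly because decisions by the study team can bias it. The same reasoning is not applied to relatedness.

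**Working it through.** **1. The plan's own figures.** The article gives no rate or sample size for adverse events. Its only sample size is for the primary endpoint: 0.8 SD, two-sided 0.05, 90% power. The exact *t*-test calculation gives 33.8, hence 34 per group (power 0.9015 at 34), and 34 / (1 − 0.15) = 40. These reproduce the stated 34 and 40. Only the 40 per arm is carried forward.

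**2. Can masking of the relatedness judgement be inferred?**

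| Party | What the article says | Masked? |
|---|---|---|
| Operator | Chooses stent and size by allocation (Stent types) | No |
| CRA role | Randomises (Procedure); monitors and reports adverse events (Trial management) | Cannot be assumed |
| CTA readers | Blinded to allocation (CTA) | Yes, but they read images |
| Assessor of relatedness | Not named | Not described |

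No party described as masked is given the task of judging relatedness.

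**3. Size, by illustration.** All event and attribution rates here are assumptions.

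- r = true risk of any event, equal in both arms, varied from 20% to 50%.
- a₁, a₂ = share of patients with an event whose event is called related, by arm.
- Apparent risk of a related event in each arm: pᵢ = r × aᵢ. The apparent ratio is p₂/p₁ = a₂/a₁, whatever r is.
- Rejection probability: the sum over all pairs of counts (x₁, x₂), each from 0 to 40, of Bin(x₁; 40, p₁) × Bin(x₂; 40, p₂), taken where the two-sided Fisher p-value is at most 0.05.

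Example at r = 40%: 40 × 0.40 = 16 patients with any event are expected in each arm. With attribution 30% v 45%, the expected related counts are 16 × 0.30 = 4.8 and 16 × 0.45 = 7.2. With 30% v 60% they are 4.8 and 9.6.

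| True risk r | 30% v 30% | 30% v 45% | 30% v 60% |
|---|---|---|---|
| 20% | 0.7% | 2.1% | 6.4% |
| 30% | 1.4% | 4.6% | 13.8% |
| 40% | 2.1% | 6.9% | 20.9% |
| 50% | 2.6% | 9.0% | 28.1% |

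The apparent ratio is 0.45/0.30 = 1.5 in the middle column and 0.60/0.30 = 2 in the last, with no true difference. The all-event comparison has equal expected counts in every row (for example 16 v 16 at r = 40%), though observed counts would vary by chance.

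**The case against.** **The article does not say who judges relatedness.** This stands. The CRA is said to monitor and report events, not to assign causality, and the full protocol (Additional file 1, not shown) may name a masked assessor. A reader might infer that relatedness is decided with the arm known. The article supports only that no masking is described.

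**No expected direction is stated.** This also stands. A reader might infer from the Background that the team expects the high-COF stent to do worse on safety. But the Background evidence concerns neointima and patency, includes two animal studies without a significant difference, and notes that human data are lacking. The objective is to investigate differences, and the primary test is two-sided.

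**The monitoring is independent.** The article describes monitoring sessions and "interim analyses every 6 months (independent from study investigators and sponsor"). Independence lessens conflict of interest, but it is not blinding, and the CRA role also randomises.

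**No adverse-event test is fixed.** True. A between-arm comparison is the natural reading of a secondary objective in a two-arm randomised trial, but it is a reading. Nothing forbids tabulating all events, and the detail of safety tables belongs to an analysis plan. What the article does fix is the outcome, and it fixes it as related events only.

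**All SAEs are reported anyway.** They go to the ethics committee. That serves oversight and does not make them an outcome by arm. It does show that the data will exist.

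**The illustration can be small.** Correct. With 30% v 45%, rejection stays below 5% at true risks of 30% or less.

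**The remedy is not free of bias.** Correct. Staff who know the arm may also detect and record non-serious events differently. SAEs are less open to this, which is why they should carry most weight.

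**Conclusion.** The concern holds as an avoidable risk of bias in a secondary safety outcome. The only adverse-event outcome named depends on a post-randomisation judgement for which no masking is described, while adverse events are already monitored without that restriction. The article does not show that any bias will occur or which arm it would favour.

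The size depends wholly on assumed rates. With 40 per arm and equal true risk of 20-50%, unequal attribution raises Fisher rejection from 0.7-2.6% to about 2-9% (30% v 45%) or 6-28% (30% v 60%). In 80 patients the distorted estimate matters more than the test, because the apparent ratio of 1.5 to 2 does not depend on the event rate.

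The primary endpoint, its blinded reading and the sample size are untouched. This is a cheap improvement of minor severity.

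**What to change.** In the Abstract (Methods) and in Secondary objectives, add all adverse events and all SAEs by randomised arm, regardless of relatedness, to the safety objective. Give most weight to the SAE comparison. Keep the device- and procedure-related events beside it.

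The cost is one more table, drawn from events the CRA already monitors, and some dilution of the display by unrelated events. Keeping the related subset in view limits that dilution.
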